### Economic Analysis

A cost-consequences analysis will compare the incremental costs of the intervention to the full spectrum of outcomes included in the study. A series of cost-effectiveness ratios will be determined rather than just one—an approach that is useful to decision-makers. The inclusion of a quality-of-life measure (AQoL-4D) enables a cost-utility analysis to be undertaken, where outcomes are expressed in generic quality-adjusted life years (QALYs), thereby allowing practical judgments to be made regarding the value-for-money credentials of the intervention. For example, in Australia, cost-effectiveness ratios falling below AUD $50,000/QALY (approximately US $35,750/QALY) are deemed good value for money [65].

The evaluation will first assess the value of any changes to the use of health care resources over the study period for both treatment arms (including costs of delivering the intervention) and then compare any antidepressant or additional costs to the outcomes achieved. While we expect medication use to decrease, we will assess the value of the use of all services (using publicly available unit costs where possible). The economic analysis will be conducted from a societal perspective, including all costs (even those outside the health sector) and productivity impacts. Secondary analyses from narrower perspectives (eg, health) will also be undertaken to address the interests of different stakeholders.

We will use standardized economic evaluation techniques, including incremental analyses of mean differences and bootstrapping, to determine CIs. Regression techniques using a net-monetary benefit framework will also be used to investigate subgroup effects and the potential predictors of differences in costs and benefits, as well as overall cost-effectiveness. If the intervention is found to be effective, we will determine the lifetime and population cost-effectiveness of the intervention using modeling techniques refined by health economists from the study team.

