### Consent

In line with International Council on Harmonisation of Technical Requirements for Registration of Pharmaceuticals for Human Use–Good Clinical Practice (ICH-GCP) [54] regulations, patients who are eligible and willing to participate are provided with a patient information sheet (PIS) that informs patients about the study purpose, their involvement in the study, data management, and their right to withdraw. The PIS also informs patients that they need to provide additional consent to allow access to their routinely collected health service use data and prescription data for the study’s health economic analysis. It is made clear that they can decline this consent without it affecting their participation in the study or the services they usually receive from their GPs. Once participants are determined to be eligible and have provided verbal agreement to take part in the trial, they can electronically consent to the study via their user account. A digital record of the consent is retained by the research team.

Participants are sent a separate PIS and consent form to allow access to their medical service use data and prescription medication data (Medicare Benefits Schedule [MBS] and Pharmaceutical Benefits Scheme [PBS] data) collected by the Australian Government. Participants are encouraged to read this information and, if they agree to participate, complete the consent form and return it to the research team using a postage-paid envelope. Participants can decline consent to access their collected health service use data and prescription data without it affecting their participation in the study.

After providing consent, all participants are asked to complete a set of baseline standardized measures to assess current mood, anxiety, beliefs about their medication, satisfaction with their current treatment and self-management, and quality of life (Table 1). These data are collected within a Research Electronic Data Capture (REDCap) [55] database embedded within the WiserAD website and linked through a unique identifier via an application programming interface. Participants who are ineligible due to low mood but keen to take part in the study will be advised to reapply for participation in 8‐12 weeks, depending on the severity of their symptoms at the time of eligibility screening.

**Table 1. T1:** Measures in the WiserAD trial.

Measure	Purpose	Time of assessment				
		Baseline	3 months	6 months	12 months	18 months

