Demographics	Gender at birth, year of birth, and postcode	✓	—^a^	—	—	—
PHQ-9^b^ [53]	Depressive symptoms	✓	✓	✓	✓	✓
GAD-7^c^ [56]	Anxiety symptoms	✓	✓	✓	✓	✓
BMQ^d^ [57]	Beliefs about medications	✓	✓	✓	✓	✓
PAM^e^ [58]	Patient activation	✓	✓	✓	✓	✓
AQoL-4D^f^ [59]	Quality of life	✓	✓	✓	✓	✓
RUQ4^g^ [60]	Health care use	✓	✓	✓	✓	✓
Signs and symptoms	Common side effects	✓	✓	✓	✓	✓
Medications	Current medications	✓	✓	✓	✓	✓
MBS^h^	Medical benefits	—	—	—	—	✓
PBS^i^	Pharmaceutical benefits	—	—	—	—	✓
AMT^j^ [61]	Accountability	✓	✓	✓	—	—
UES-SF^k^ [62]	User engagement	✓	✓	✓	✓	✓

a Not applicable.

b PHQ-9: Patient Health Questionnaire-9.

c GAD-7: Generalized Anxiety Disorder-7.

d BMQ: Beliefs About Medicines.

e PAM: Patient Activation Measure.

f AQoL-4D: Assessment of Quality of Life Scale.

g RUQ4: Resource Use Questionnaire-4.

h MBS: Medicare Benefits Schedule.

i PBS: Pharmaceutical Benefits Scheme.

j AMT: Accountability Measurement Tool.

k UES-SF: User Engagement Scale-Short Form.

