### Economic Evaluation

A comprehensive economic evaluation of quality of life and health care use (medical and pharmaceutical) will be conducted using a study-specific self-report Resource Use Questionnaire-4 (RUQ4) adapted from a questionnaire used in a previous trial conducted by our group [64,65]. The RUQ4 will record the type, frequency, and duration of health service use by participants through direct and indirect cost savings in the preceding 3 months and will be collected at 3, 6, 12, and 18 months. Through the assessment of measures of social activities, such as work and benefits, the impact of mental health can be assessed. The RUQ4 will be integrated into the website and will follow a conditional logic model, where subsequent questions will only be presented if a participant’s previous response requires further information. This approach is intended to help with the completion of the questionnaire by reducing the burden on participants.

The Assessment of Quality of Life-4D (AQoL-4D), a validated measure, will be used to assess the impact of mental and physical health on everyday quality of life [59]. For participants who provide additional consent, reliable health service use data will be obtained from the MBS and PBS. These records provide supporting data and information regarding primary and secondary care visits and prescription medications through Australia’s universal health care system.

The actual cost of the intervention will be determined and captured using financial and provider records.

Mediators will be measured at baseline and 3, 6, 12, and 18 months. To understand possible mediators, the following will be recorded: (1) participant beliefs and motivations related to their relationships with medications, which will be measured using the Beliefs about Medicines Questionnaire (BMQ) [57]; (2) accountability and engagement, which will be measured using the Accountability Measurement Tool (AMT) [61] and User Engagement Scale-Short Form (UES-SF) [62], respectively; and (3) signs and symptoms typically associated with reducing antidepressants, which will be assessed (text responses) during contact with the WiserAD research nurse.

Other measures include data from the daily tracker, retention, and compliance with the tapering schedule (assessed using analytic data collected on the WiserAD website).

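### The economic analysis names no baseline term for costs or QALYs, although Table 1 schedules both measures at baseline, and the text on the resource-use questionnaire omits that baseline visit

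*Protocol article*

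**What the plan says.** **Economic estimator.** Economic Analysis promises standard techniques, among them "incremental analyses of mean differences and bootstrapping, to determine CIs". The next sentence adds regression in a net-monetary-benefit framework, for subgroups, for predictors of cost and benefit differences, and for overall cost-effectiveness. No covariate is named for either approach.

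**Baseline data.** Table 1 ticks the AQoL-4D at baseline and at all four follow-ups. It ticks the RUQ4 (purpose: "Health care use") at the same five visits. The Consent section names quality of life among the baseline measures. It does not name resource use, but it refers the reader to Table 1.

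**RUQ4 timing in the text.** Economic Evaluation says that the RUQ4 covers service use "in the preceding 3 months and will be collected at 3, 6, 12, and 18 months". Baseline is not in that list.

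**Clinical outcomes, for contrast.** The statistical methods section for the primary and secondary objectives says that regressions adjust for baseline outcome measures where appropriate. For continuous secondary outcomes, month 0 is part of the response and the baseline means are constrained to be equal. The Objectives section lists the economic objectives separately, and the AQoL-4D is not among the secondary outcomes, so this wording does not clearly extend to QALYs or costs.

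**The concern.** Baseline utility is usually a strong predictor of later utility. If QALYs are computed as an area under the utility curve, it is also the first point of that area. A between-arm difference in utility that exists by chance at month 0 therefore carries into the QALY difference unless the estimate is conditioned on it. The same holds for service use and later costs. The article cites AUD 50,000 per QALY as a benchmark for value for money, so shifts of a few hundredths of a QALY can matter to the conclusion.

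The RUQ4 timing matters here because baseline RUQ4 cost is the natural covariate for the cost comparison. The alternative source, MBS and PBS records, needs separate optional consent and is ticked only at 18 months. It is described as covering care visits and prescriptions, whereas the main perspective is societal and includes productivity. If the RUQ4 was not taken at baseline, the cost adjustment may not be available for all participants.

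**Working it through.** **Step 1: passages side by side**

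| Item | Table 1 | Text |
|---|---|---|
| AQoL-4D at baseline | ticked | quality of life named at baseline (Consent) |
| RUQ4 at baseline | ticked | "will be collected at 3, 6, 12, and 18 months" (Economic Evaluation) |
| Baseline term, clinical outcomes | n/a | stated |
| Baseline term, costs and QALYs | n/a | none stated |

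Later in Economic Evaluation the mediators are timed with baseline named, so its absence from the RUQ4 sentence is noticeable. On the other side, Secondary Outcomes lists the GAD-7 at follow-up visits only, although Table 1 ticks it at baseline and the model for continuous outcomes includes month 0. The article does sometimes list only follow-up visits for a measure that is also taken at baseline.

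**Step 2: inputs**

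- From the document: visits at 0, 3, 6, 12 and 18 months; 170 per arm; up to 50% attrition at 6 months; AUD 50,000 per QALY.
- Assumed, because the document gives no value: utility SD 0.20 to 0.25 at every visit; correlation ρ of 0.5 to 0.7 between any two visits; QALYs by the trapezoid rule.

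The document states no figure for the economic analysis to reproduce. Its sample size does reproduce: 36% versus 16% at 80% power, with continuity correction, gives 85 per arm, and 85 / 0.5 = 170.

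**Step 3: QALY weights**

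Trapezoid weights in years are 0.125, 0.25, 0.375, 0.5 and 0.25, which sum to 1.5. Baseline has 0.125 and the follow-up visits together have 1.375.

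**Step 4: effect of a one-SE baseline imbalance**

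SE of the baseline difference = SD × √(2/n). Shift in the QALY difference = SE × (0.125 + 1.375ρ). The bracket is 0.8125 at ρ = 0.5 and 1.0875 at ρ = 0.7.

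| n per arm | SD | ρ | SE | QALY shift | At AUD 50,000 |
|---|---|---|---|---|---|
| 170 | 0.20 | 0.5 | 0.0217 | 0.018 | 881 |
| 170 | 0.25 | 0.7 | 0.0271 | 0.029 | 1,474 |
| 85 | 0.20 | 0.5 | 0.0307 | 0.025 | 1,246 |
| 85 | 0.25 | 0.7 | 0.0383 | 0.042 | 2,085 |

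The last column is AUD per person. With an SD of 0.15 and ρ = 0.5 at 170 per arm, the shift falls to 0.013 (AUD 661).

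**Step 5: variance removed by adjustment**

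The sum of squared weights is 0.53125 and the squared sum is 2.25, so the cross-product part is 2.25 − 0.53125 = 1.71875. In units of SD², Var(QALY) = 0.53125 + 1.71875ρ. The share removed is (0.125 + 1.375ρ)² / Var(QALY).

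- ρ = 0.5: 0.8125² / 1.3906 = 0.660 / 1.391 = 47%.
- ρ = 0.7: 1.0875² / 1.7344 = 1.183 / 1.734 = 68%.

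The standard error of the QALY difference would fall by 1 − √(1 − 0.475) = 28% and 1 − √(1 − 0.682) = 44%, respectively.

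**The case against.** A reader might infer that the plan compares raw means and that baseline imbalance passes straight into the cost-utility result. The document does not support that. It never calls the means raw or unadjusted. A mean difference can be regression-adjusted and then bootstrapped, and the list of techniques is not presented as complete. The net-benefit regression also covers overall cost-effectiveness and could include baseline covariates. The stated aim of valuing changes in resource use over the study period is at least compatible with using a baseline value. Covariate lists are often left to a fuller plan. All of this stands, and it limits the point to what the article leaves unstated.

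A reader might also infer bias. Under randomisation, chance imbalance does not bias an unadjusted comparison systematically, and the bootstrap interval already reflects that variability. The cost is lost precision, plus conditional bias in the sample actually drawn. It would also be wrong to say that baseline utility plays no part: under the trapezoid rule it is the first point of the QALY area.

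On the RUQ4, the text does not say that baseline collection was dropped, and the GAD-7 is listed in the same way. Alone, that mismatch is an editorial alignment.

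Finally, the 85-per-arm rows apply 6-month attrition to an 18-month QALY and treat imbalance among responders as pure chance, although loss on that scale may be selective. They are indicative only.

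What remains is that the main incremental estimate, read plainly, is a mean difference with no baseline term, with regression introduced as an addition. The clinical section of the same article states its baseline handling.

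**Conclusion.** The point holds in limited form. The economic section names no baseline term for costs or QALYs although the measures are scheduled in both arms, and the RUQ4 text omits a baseline visit that Table 1 ticks. If the main estimate is made without baseline terms, a one-SE chance imbalance would move the QALY difference by about 0.018 to 0.029 at 170 per arm. Adjustment would remove roughly half to two thirds of the QALY variance (47% to 68%). These sizes rest on the assumed SD and correlation, equal correlation between all visits, and complete follow-up. The primary clinical outcome and its sample size are unaffected. This is a gain in precision and clarity, not the correction of a demonstrated error in the estimate.

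**What to change.** 1. In Economic Evaluation, add baseline to the RUQ4 collection times so that they match Table 1. If the RUQ4 was not in fact taken at baseline, correct Table 1 instead and say so.
2. In Economic Analysis, state that incremental QALYs come from a regression on arm adjusted for baseline AQoL-4D utility. State that incremental costs come from a regression on arm adjusted for baseline RUQ4 cost, provided it was collected as scheduled.
3. Apply the bootstrap to the adjusted estimates, and use the same covariates in the net-monetary-benefit model.

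The cost is wording only, if collection followed Table 1. Recruitment closed in January 2026, so a missing baseline RUQ4 could no longer be collected. In that case the QALY adjustment still stands, and the report should state that costs were not adjusted for baseline RUQ4 cost.

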### Monitoring

In addition to monthly working committee meetings, the trial will be monitored quarterly by a trial steering committee. This committee comprises the chief and associate investigators, including a biostatistician and a health economist. A research fellow and the trial manager will also attend meetings. An independent data monitoring committee with an established charter will meet regularly to track progress and recruitment, review AEs, and monitor the protocol design. The data monitoring committee is comprised of experts in the fields of clinical trials, primary care, and biostatistics, and it will provide feedback to the trial steering committee.

### Risk Management

The clinical care of all participants will be managed by their treating GPs throughout the trial.

There is no planned assessment of safety within the study design, and unless participants report any intercurrent illnesses or AEs directly to the study team, it is unlikely that these will be systematically recorded. However, if a participant scores 2 or 3 on the PHQ-9 item “thoughts that you would be better off dead or of hurting yourself in some way,” the researcher will flag the finding or an online recommendation will be provided to consult their GP to discuss the finding. The research team will also be notified of this response and will attempt to contact the participant. Moreover, the trial manager or WiserAD research nurse will break the identity code and contact the GP directly to inform them about the finding and recommend that they contact the participant.

Participants experiencing a higher number of symptoms than previously indicated or showing signs of worsening mood will be contacted by the WiserAD research nurse for a structured risk assessment. Follow-up protocols, which include alerting the GP, will be triggered for participants identified to be at high risk of self-harm. A consultant psychiatrist from the chief investigator team will be available to provide psychiatric input upon request by the study team or participating GPs. Regardless of their allocation, all participants will be provided with the number for Lifeline and will be encouraged to discuss any concerns with their GPs. Finally, for participants in the attention control arm, involvement in the study is not expected to pose risks beyond those of usual GP care, as these participants will not be advised to discontinue their antidepressant medication and will continue to receive treatment as usual.

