The second eligibility screening confirms the following: (1) no or mild depressive symptoms (defined as having a total PHQ-9 score of <10 for depressive symptoms) [53]; (2) low risk of suicide or self-harm (PHQ-9) [53]; (3) agreement to be randomized in the study; and (4) willingness to provide informed consent.

For individuals who do not meet the eligibility criteria, no personal data are retained, except for demographics used to characterize the sample.

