### Randomization and Allocation Concealment

Once eligibility is confirmed, consent is provided, and baseline measures are completed, participant details are entered into a randomization system embedded within the WiserAD website. Allocation is triggered when the participant confirms completion of the REDCap baseline assessment by clicking a button on the WiserAD website. Participants are assigned with equal probability to the 2 trial arms using a computer-generated allocation sequence, with stratification by general practice for participants identified via general practices (recruitment strategy 1) or by state of residence for self-referring participants (recruitment strategy 2). An allocation sequence is generated using random permuted block sizes within each stratum. To ensure concealment, the block sizes are not disclosed until after trial recruitment is complete. A trial statistician who is not involved in participant recruitment or data collection generates a random allocation schedule. Research staff who are involved in recruitment and intervention delivery may be aware of participant allocation when necessary for trial conduct. Data analysts and other research team members who do not require access to allocation information remain blinded until completion of the analysis. GPs are not informed about participants’ treatment allocations; however, complete blinding of GPs is not possible as they may make inferences about allocation. This is not expected to impact trial conduct, outcomes, or analysis integrity. The trial manager does not communicate with the research team about participant allocation during the trial, and any cases of unblinding are recorded.

The random allocation sequence is embedded within the website, ensuring allocation concealment. Only the trial manager or their nominee has password access to the random allocation of participants. Participants are not blinded to their trial arm assignment. Trial arm allocation remains concealed from the research team until recruitment and follow-up are complete and the cleaned dataset is locked for analysis.

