## Discussion

### Anticipated Findings

The WiserAD IST aims to increase the proportion of participants who successfully discontinue long-term antidepressant use while maintaining mental health at 6 months compared with usual care. The trial also examines whether anxiety symptoms are maintained, patient activation increases, and beliefs about medication shift toward a neutral stance. The trial describes patterns of antidepressant use and longer-term management. If the WiserAD IST maintains patient mental health while improving appropriate discontinuation or dose reduction, it will offer a practicable, patient-centered pathway for deprescribing that balances safety with scalability. If outcomes are modest, quantitative and qualitative findings will indicate which components require strengthening to achieve larger, sustained reductions in inappropriate long-term antidepressant use.

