### Conclusions

The WiserAD IST is a novel, co-designed, patient-facing digital tool that combines personalized tapering, educational materials, decision aids, and structured nurse support. This novel IST is scalable to routine primary care practice while having minimal impact on GP workload and providing deprescribing guidelines and practical support. The WiserAD IST facilitates safe and appropriate dose reduction or discontinuation without clinically meaningful worsening of depressive symptoms. Alongside the outcome data, the embedded realist evaluation identifies the mechanisms for implementation of the IST in practice. This research holds high potential to inform Australian mental health policy and clinical practice.

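### The protocol plans no safety assessment yet states as fact that the tool is safe; a by-arm count of the self-harm item, already scheduled in both arms, would be a cheap improvement

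*Protocol article*

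**What the plan says.** All references are to the protocol article.

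- **Risk Management.** "There is no planned assessment of safety within the study design". On adverse events: "unless participants report any intercurrent illnesses or AEs directly to the study team, it is unlikely that these will be systematically recorded". An individual alert follows "if a participant scores 2 or 3 on the PHQ-9 item" about self-harm: the participant is pointed to the GP, the team tries to make contact, and the trial manager or nurse breaks the code and informs the GP.
- **AE Reporting and Monitoring.** Events that do come to light are recorded under ICH-GCP and reviewed by the steering committee, and the data monitoring committee reviews adverse events.
- **Table 1 and Outcomes (Overview).** The PHQ-9 is scheduled at baseline and at 3, 6, 12 and 18 months in both arms, by survey link or by phone. A signs-and-symptoms row ("Common side effects") has the same timetable.
- **Primary and Secondary Outcomes.** The PHQ-9 enters as a total below 10 inside the cessation composite. Mean GAD-7 is compared by arm at each follow-up. No comparison of the self-harm item is listed.
- **Randomization Codes.** After data collection, the frequency of unblinding will be compared between arms.
- **Conclusions.** "The WiserAD IST facilitates safe and appropriate dose reduction or discontinuation". The sentence goes on to rule out clinically meaningful worsening of depressive symptoms.
- **Anticipated Findings.** The tool would offer a "patient-centered pathway for deprescribing that balances safety with scalability". This is conditional on mental health being maintained while discontinuation or dose reduction improves.

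**The concern.** The trial supports people in stopping a psychiatric drug, and it enrols only people screened as being at low risk of self-harm. Whether such thoughts emerge more often under supported tapering than under usual care is therefore a natural question. The absence of a safety assessment is a declared design choice, not silence that an unseen SAP might fill. Under the analyses named, the trial would not report that comparison, although the answers are already scheduled in both arms. A firm statement that the tool is safe would then stand beside a stated decision not to assess safety.

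**Working it through.** **1. Does any named comparison isolate self-harm?**

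- *Primary composite.* Failure can mean continued use, PHQ-9 of 10 or more, or both, so it does not separate relapse from not stopping. A 2 or 3 on the self-harm item is compatible with a total below 10, so such a person can count as a success.
- *GAD-7.* Compared by arm, but it measures anxiety.
- *Unblinding comparison.* It may include code breaks triggered by self-harm alerts, but mixed with other code breaks and without separating them.
- *Volunteered adverse events.* Nurse contact, the monitored daily tracker and the extra PHQ-9s it can trigger are described for the intervention arm only. More contact can yield more reports, so a by-arm count of them would be hard to interpret.
- *Signs and symptoms.* Table 1 schedules the row at each follow-up, but the Economic Evaluation section describes text responses taken at nurse contact, so equal collection is uncertain.
- *Self-harm item on scheduled PHQ-9s.* Same timetable in both arms. After randomisation its only named use as a separate item is the individual alert.

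**2. How many responders?** Inputs from Sample Size: 170 per arm, 36% vs 16%, 80% power, two-sided 5%, 50% attrition.

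n0 = [1.960√(2 × 0.26 × 0.74) + 0.842√(0.36 × 0.64 + 0.16 × 0.84)]² / 0.20² = 74.3. With continuity correction, n = (n0/4)[1 + √(1 + 4/(0.20 n0))]² = 84.02, rounded up to 85. Then 85/0.5 = 170 per arm, or 340. The stated figure reproduces, and 170 × 0.5 = **85 responders per arm** at 6 months.

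**3. How many events?** The document gives no rate for scores of 2 or 3. Assuming 1% to 5%: 85 × 0.01 = 0.85 and 85 × 0.05 = 4.25, so about 1 to 4 per arm at that visit.

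**4. What could the table show?** Newcombe score 95% interval for the risk difference d = p1 − p2, with Wilson limits (l, u) for each arm: lower = d − √[(p1 − l1)² + (u2 − p2)²]; upper = d + √[(u1 − p1)² + (p2 − l2)²].

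Example, 4 vs 0: Wilson limits are 1.85% to 11.48% and 0% to 4.32%. Lower = 4.71 − √(2.86² + 4.32²) ≈ −0.5; upper = 4.71 + 6.78 ≈ 11.5.

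| Events of 85, per arm | Difference (points) | 95% CI |
|---|---|---|
| 0 vs 0 | 0 | −4.3 to 4.3 |
| 2 vs 2 | 0 | −6.1 to 6.1 |
| 4 vs 4 | 0 | −7.4 to 7.4 |
| 4 vs 2 | 2.4 | −4.1 to 9.3 |
| 4 vs 0 | 4.7 | −0.5 to 11.5 |
| 5 vs 0 | 5.9 | 0.4 to 13.0 |

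The exact two-sided upper limit for 0 of 85 is 1 − 0.025^(1/85) = 4.2%.

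**5. How far could non-response mislead?** Participants know their arm, so response may differ. Suppose the true rate p is equal in both arms and overall response is 0.5. In one arm, affected people answer at k = 0.5 times the rate r of others (an assumption). Then r = 0.5/[(1 − p) + kp] and the observed rate is k·r·p/0.5. For p = 1%, 2% and 5% this is 0.5%, 1.0% and 2.6%, a spurious gap of 0.5, 1.0 and 2.4 points.

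**The case against.** The strongest reply has four parts.

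*Mental health is compared by arm.* This stands in part. The Conclusions sentence ties safety to depression not worsening, and the composite and GAD-7 bear on mental health. A reader might infer that the trial has no by-arm data at all bearing on harm, or that adverse events are not recorded. The document does not support either reading. What is missing is narrower: a comparison of self-harm, and one of relapse apart from continued use.

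*Anticipated Findings is conditional.* This stands in full. A reader might take that section as a second assertion of safety, but it says only what would follow if mental health were maintained. The conflict is with Conclusions alone.

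*A descriptive item count belongs in the SAP, which is not shown.* Partly right: the SAP is a proper home for the table, and the Risk Management sentence does not forbid one. But that sentence declares that no safety assessment is planned, and the topics which Statistical Methods names for the SAP do not include safety. If the SAP does contain such a table, the protocol sentence is out of step with it.

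*With so few events, the table says little.* The small numbers are real, and a reader might hope the table could show the tool to be safe; it cannot. They are a reason to publish the interval and to soften the claim, not a reason to leave the item unreported.

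**Conclusion.** The point holds as a cheap improvement. The protocol disclaims any planned safety assessment while Conclusions presents safety as established before results, and no named analysis compares self-harm by arm. It is not evidence that the tool is unsafe, nor that oversight of individual participants is lacking.

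The gain is modest: about 1 to 4 events per arm at 6 months, with intervals of roughly ±4 to ±7 points when the counts are equal. These figures assume the stated 50% response and a 1% to 5% rate of scores 2 or 3. The non-response gap of up to 2.4 points further assumes that affected people in one arm answer half as often as others. The textual finding depends on none of these assumptions.

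**What to change.** Before analysis starts:

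1. Replace the Risk Management statement, or add to the SAP, one descriptive safety outcome: by randomised arm, the number and proportion of responders scoring 2 or 3 on the PHQ-9 self-harm item at 3, 6, 12 and 18 months and at any scheduled visit, whether or not they have stopped. Give the risk difference with a score or exact 95% CI. Count only the scheduled Table 1 questionnaires, not the extra PHQ-9s prompted by the tracker. Show response rates by arm beside it.
2. Reword the Conclusions sentence as a hypothesis, since the table cannot establish safety and zero events would not prove it.

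The primary outcome and the individual alert stay as they are.

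**Cost.** One outcome definition, one table and one or two changed sentences, with no new data, visits or staff. The drawbacks are few events, wide intervals and possible bias from about 50% non-response. Recruitment has closed, so a protocol change may need an ethics amendment. Placing the table in the SAP, which is due before any analysis, could avoid that.
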